## Abstract

**Background:**

Many individuals with intellectual disability (ID) have not learnt basic reading skills by the time that they reach adulthood, potentially limiting their access to critical information. READ-IT is an online reading programme developed from the Headsprout® Early Reading (HER®) intervention and supplemented by support strategies tailored for adults with ID. HER® has been successfully used to teach adults with ID to read in a forensic setting by trained staff. The aim of this study is to assess the feasibility of delivering READ-IT to adults with ID by family carers/support workers and will assess whether it would be feasible to conduct a later definitive randomised controlled trial (RCT) of the effectiveness of the programme. The study will aim to contribute to the evidence base on improving outcomes for adults with ID and their caregivers.

**Methods:**

This study is a feasibility RCT, with embedded process evaluation. Forty-eight adults with ID will be recruited and allocated to intervention: control on a 1:1 basis. Intervention families will be offered the READ-IT programme immediately, continuing to receive usual practice and control participants will be offered the opportunity to receive READ-IT at the end of the trial follow-up period and will continue to receive usual practice. Data will be collected at baseline and 6 months post-randomisation.

**Discussion:**

The results of this study will inform a potential future definitive trial, to evaluate the effectiveness of READ-IT to improve reading skills. Such a trial would have significant scientific impact internationally in the intellectual disability field.

**Trial registration:**

ISRCTN11409097

**Supplementary Information:**

The online version contains supplementary material available at 10.1186/s40814-022-00972-x.

## Background

Reading is an essential skill for daily life and a pre-requisite for independent living [1, 2]. Many individuals with ID (known as learning disability in UK health and social care services) have not learnt basic reading skills by the time that they are adults [3] and, as a cohort, have poor literacy skills [2]. An inability to read potentially limits a person’s access to critical information relevant to their daily lives and has been cited as a secondary impact of ID and the cause of significant additional limitations [4].

One of the ways of addressing a lack of reading skills is to make information more accessible using, for example, Easy Read formats. Whilst this may be effective for some, recent research suggests that this is not always the case [5]. Easy Read may be presented in a way that cannot be tailored to meet individual needs [6, 7], and, critically it does not teach a person to read—a skill which may significantly improve that person’s independence, quality of life and overall participation in society [2] with implications both for the person and for those who support them. It should also be noted that what is meant by ‘Easy Read’ is not standardised, including the inclusion or exclusion of text accompanying pictures. Research evidence indicates that young people with ID want the same things as anyone else—to be able to live independently if they so choose, to have friends, a family and to have a job [8]. However, the gap between aspirations and outcomes is much greater amongst people with ID than the wider population and, as they move into adulthood, that gap gets wider [8]. The ability to read is a key to achieving many of these aspirations.

The relationship between levels of proficiency in literacy and employment outcomes for example is well established for the population as a whole [9], and poor literacy skills have been identified as a barrier to employment for people with ID [10]. Even if the ability to read is not a job requirement, it is needed to read job advertisements, complete application forms and to be able to follow procedures and instructions at work.

Making healthy lifestyle decisions is another example. A recently conducted study analysing primary health-care data on 1,424,378 adults found, even when accounting for factors such as neighbourhood deprivation, increased co-morbidity with other healthcare issues and lower mortality rates in the cohort of adults with ID compared to the general population [11]. Reducing this inequality requires initiatives tailored for adults with ID. One of the problems, however, is access to information that might directly empower adults with ID themselves which in turn depends upon health literacy [12]. Many policy initiatives directed at providing that information to the general population are unlikely to benefit people with ID and, as noted above, attempts to increase the accessibility of information are not always effective. This often places a responsibility on carers to mediate access to information.

There is also an emerging body of research that suggests that being able to read can increase the quality of life of individuals with ID helping with additional skills development such as problem-solving, making informed choices and increasing access to the community [2, 13].

There is relatively little research into the reading skills of adults with ID and even less on effective interventions. In part, this has been because of a non-evidence-based perception that it is not possible to teach people with ID to read, whatever their age [14] and more generally that the ability to learn plateaus in adults with ID [15, 16]. Furthermore, the focus of support as children with ID gets older and transition to adulthood often moves away from an academic to more functional curricula with an emphasis on the communication, social and daily living skills deemed necessary for adult life [17]. More recently, these assumptions have been challenged. Studies have shown that it is possible with appropriate teaching and learning strategies, to teach people with ID reading skills [18–20] and, although learning may progress more slowly, that it is possible for adults with ID to continue to learn into adulthood, including learning to read [21, 22].

There has been, however, no high-quality research evidence supported by a randomised controlled trial (RCT) of the effectiveness of strategies to teach adults with ID to read. Much of the research into improved reading skills is with typically developing children. In the UK, the education endowment foundation (EEF) recommends implementing a systematic phonics programme for children, and, because learning to read is not an innate ability, Gough and Hillinger [23] recommended teaching strategies include repeated instruction and opportunities to practice learning to decode text. A systematic review of the literature of teaching strategies to improve reading skills in people with ID concluded that intense practice and instruction is needed and that it should be provided ‘explicitly, systematically, and consistently’ and found no RCTs of reading interventions for adults with ID [24].

HER® is an online reading programme which incorporates sight reading and explicit systematic instruction on the three early reading skills involved in decoding that are part of five critical areas of learning to read: phonemic awareness, phonics and fluency (the other two areas being vocabulary and text comprehension). The ability to decode is an essential component to becoming a proficient reader. HER® [25] involves repeated opportunities to practice decoding and sounding out words, working at the pace of the individual and to suit their needs through 80 online episodes/sessions. HER® has been shown to be effective with typically developing children in large scale implementation studies, including a RCT in the USA [26]. A small UK-based RCT also suggests positive outcomes for HER® versus the usual teaching of reading with children with mild to moderate intellectual disabilities in a mainstream school setting [27]. Our pilot research with small numbers of children in special schools and special resource units has suggested that, with the inclusion of some additional support strategies, HER® can also be effective for children with ID [27–29] especially (but not limited to) those children with the following pre-requisite skills: able to speak clearly, can verbally repeat words modelled to them, are capable of following simple instructions, and have basic computer/touch screen skills (i.e. are able to move and click a mouse appropriately—mouse skills can also be directly taught to increase access). Teaching that is delivered online rather than face-to-face may be easier for people of any age with ID to access, offers a learning experience tailored to their needs and may be more cost effective compared to one-to-one instruction from trained professionals. Critically, it also offers access to more people than can be achieved through one-to-one or even small group instruction.

In the first study to explore the use of HER® to teach basic reading skills to adults with a mild ID, the feasibility of running the intervention in a forensic setting was demonstrated and showed improved decoding skills critical to reading and self-concept scores for participants [3]. No adaptations were needed for the online programme, but trained staff were available to supervise the programme and it was easy to schedule it into the working day. However, working in a secure setting is not the same as typical community and social care settings for people with ID.

A manual incorporating additional support strategies that can be used alongside the standard HER® online programme for anyone helping children with ID to read in home or school settings has been developed by the research team. It has been specifically developed for teachers, teaching assistants and parents mediating their pupil/child’s programme, but will be adapted for support workers and family carers working with adults with ID.

There is a current gap in the availability of suitable reading programmes for adults with ID, in the evidence base around teaching adults with ID new skills and, critically, in the potential impact that teaching adults to read has on their ability to access information relevant to healthy lifestyles, independence, informed choice and ultimately quality of life. READ-IT, and the current research proposal, directly address that gap.

## Methods/design

### Objectives/aim

The aim of this feasibility RCT is to assess the feasibility of delivering a reading intervention to adults with ID by family carers/support workers. The study will aim to contribute to the evidence base on improving outcomes for adults with ID and their caregivers. Importantly, the study will inform a potential, definitive RCT of the effectiveness and cost-effectiveness of the programme. The study primary objective is to examine whether READ-IT can be *delivered* successfully by community support workers/family carers. The study secondary objective is to assess whether it would be feasible to conduct a later definitive RCT of the effectiveness and cost effectiveness of READ-IT.

### Study design

The study is a 2-arm, randomised controlled trial, with 1:1 randomisation using randomly permuted blocks, stratified by setting type (family home vs. other social care setting).

The study will be composed of three stages:

### Stage 1: Intervention refinement and development.

A new intervention (READ-IT) will be developed by further adapting the HER® support manual specifically for use with support workers and family carers of adults and detailing a supervision/mentoring process during the intervention delivery. The intervention will be capable of being delivered in full remotely—a critical factor in study development in a COVID-19 environment. Stage 1 will also include the development of a protocol for obtaining informed consent and data collection remotely and an adaptation for online delivery of all measures used in data collection. These and the procedure for obtaining informed consent will be developed and piloted using public and participant involvement (PPI).

### Stage 2: Feasibility study

The intervention arm participants will participate in an online reading programme (HER®) supplemented by additional support strategies tailored for adults with ID. Support workers and carers will receive a half-day training (delivered remotely) and be given a copy of the support manual. All support workers and family carers will in addition be offered bi-weekly ‘phone-in’ help sessions over the duration of the intervention. The control arm participants will experience usual practice in relation to the support of their reading and will have access to the (HER®) programme after 12 months; however, HER® training or mentoring will not be available to the control arm participants. Baseline measures for all participants will be conducted remotely prior to randomisation and repeated 6 months post randomisation. Selected participants will be approached 6 months post randomisation to take part in a qualitative study designed to address the progression criteria that will not otherwise be clear from other data collected.

### Stage 3: Logic model/full trial protocol

The findings from the feasibility study will be used to review and refine a logic model and, subject to the progression criteria being met, will lead to the development of a protocol for a full trial. This will be achieved through additional PPI input and with the advisory group.

#### Study setting

Individuals will be recruited from family homes, independent living and small group settings (e.g. supported living and residential homes). Settings for people likely to be eligible (those with mild to moderate ID) are most likely to be individual (with their family, or in independent living). This is a single site study.

#### Site selection

This is a single site study and will be carried out at University of Warwick, under the supervision of the Chief Investigator.

#### Participant selection

Individuals will be recruited from family homes, independent living and small group settings (e.g., supported living and residential homes). Families will be directed to the study team by service provider organisations in their local area following a flexible multi-point recruitment method including via targeted service provider organisations, practitioner fora, local and national charitable support organisations, local parent carer fora and self-referral. The strategy is aimed to be flexible and collaborative and information will be gathered regarding the most effective participant identification processes to inform a definitive trial. All potential participants will have been provided with a participant information sheet and will have confirmed interest in participating in the study either directly with the service provider organisation or by returning a completed reply slip to the study team. Potential participants will be contacted by study team researchers to arrange a short screening/recruitment interview, via videoconferencing. Participants are eligible for the study if they meet all of the inclusion criteria and none of the exclusion criteria apply.

#### Eligibility criteria

##### Inclusion criteria

Adults administratively defined as having an ID (i.e. through receipt of/being known to services) who:have the capacity to give informed consenthave a level of competence in understanding English suitable to access Headsprout® Early Reading programme. This is assessed via a placement assessment that is provided by HER® to assess where within the intervention the individual is best advised to start and assesses upper-reading ability.can sound out words (although *degree* of articulation will not be a factor). (Sounding out words is a requirement of the HER® component of the intervention).have access to appropriate internet-enabled technologyeither have basic mouse skills, or the capacity to be taught basic mouse skillsare living in a setting in which they are getting daily living skills support supported by a support worker/family carerhave access to a supporter who is themselves able to read and willing to support the individual for the duration of the study

##### Exclusion criteria

Adults with ID with visual impairments are severe enough to limit their access to computer-based technology even with adaptations. Adults with ID whose reading skills are too proficient to benefit from the programme, this is assessed by a placement assessment that is provided by HER®.

#### Intervention

The intervention arm participants will participate in an online reading programme (HER®) supplemented by additional support strategies tailored for adults with ID: READ-IT. HER® has been successfully used to teach adults with ID to read. In a pilot study [3], no adaptations were needed to the online programme. However, the intervention was mediated by trained staff who provided additional support when necessary to the participants. HER® has also been successfully used to teach children with ID, again without any adjustments to the programme itself (which is a commercially available product) but using other additional supports and adaptations. These adaptations have been fully described in a manual, developed by our team, for teachers, teaching assistants and parents mediating the reading intervention. A new intervention (READ-IT) will be developed by further developing the adaptations/support manual specifically for support workers and family carers so that those supporting adults with ID are able, in turn to assist with the reading intervention, and detailing a supervision/mentoring process during the intervention delivery. The intervention will be provided remotely in the participant’s home or day care centre. The adaptation of the support manual will be achieved through a PPI model in collaboration with Mencap who is the social care and PPI partner. The research team will also develop a fidelity framework to identify both the fidelity factors included in the HER® programme itself as well as any additional factors associated with adherence to the support manual and engagement with the supervision/mentoring process.

The HER® programme consists of 80 online episodes delivered in sessions of approximately 20‑25 min. HER® recommends between 3 and 6 sessions of 20 to 25 min per week. READ-IT will therefore be delivered on average 16‑20 weeks. Following recruitment and randomisation, support workers/family carers in the intervention group will be invited to attend a half-day remote training workshop. The purpose of training will be to demonstrate how the HER® online programme works and how the support manual can be used by support workers/family carers to help the person that they are supporting. Two options for training dates each month will be offered. Support workers and carers will be given a copy of the support manual and a unique code to access the HER® programme. All support workers and family carers will, in addition, be offered bi-weekly phone-in help sessions over the duration of the intervention. The intervention for each participant will begin once their support worker/family carer has completed the training.

#### Usual practice/comparator

The comparator intervention will be usual practice (UP) with waitlist READ-IT. However, no HER® training or support will be available to the control arm participants during the study period.

#### Retention strategy

To maintain engagement, encourage retention and to thank participants for their time, £20 per participant will be provided per adult during both the initial survey and again at the 6-month point. Support workers/family carers will also be offered £10 during both the initial survey and again at the 6-month point [30]. Participants taking part in qualitative interviews will also be provided with a £20 voucher to thank them for their time [30]. Contact details will be collected during recruitment, and participants will be reminded by email and text message when a data collection follow-up is due.

#### Sample size calculation

A total of 48 individuals will be recruited (randomising 24 per arm). As this is a feasibility study, and the purpose is to provide estimates of key parameters for a future trial rather than to power the current study to detect statistically significant differences, a formal a priori power calculation will not be conducted [31]. However, recruiting 48 participants will provide a certain level of precision around a 95% confidence interval. For example, if 80% of participants provide outcome data at follow-up, the 95% confidence interval around the percentage can be estimated within +/− 11% (i.e. 69 to 91%).

#### Outcomes—spirit figure

The study primary objective is to examine whether READ-IT can be *delivered* successfully by community support workers/family carers. The feasibility of using a range of established outcome measures, proposed to test the intervention in a main trial, will be assessed:Dynamic indicators of basic early literacy skills (DIBELS) which assesses the decoding skills involved in readingA measure of reading self-efficacy (and carer efficacy in supporting the person to read), these will be designed as part of the patient and public involvement (PPI) workshopsQuality of life measures for the person with ID: EQ5D-3L (health-related quality of life), the personal well-being index intellectual disability version, completed by the person with ID and the family member/support staff memberThe version of the client service receipt inventory (CSRI) used in recent ID trials will be used to examine the feasibility of collecting these data for a future health economics analysis, primarily from carers/support staff

The following will also be assessed:5.Adherence to the READ-IT intervention6.Fidelity of READ-IT intervention delivery and the most effective measure to assess fidelity

Please see Table 1 for details and timings of all outcome measures (SPIRIT figure) and Additional file 1 for SPIRIT checklist.The study secondary objective is to assess whether it would be feasible to conduct a later definitive RCT of the effectiveness and cost effectiveness of READ-IT. The secondary objective will be assessed by reviewing: Recruitment rates and effectiveness of recruitment pathways and randomisationStudy retention ratesAssessment of the barriers and facilitating factors for recruitment, engagement and intervention delivery from the perspective of all stakeholdersMeasurement of usual practiceAcceptability of the primary outcome measures

**Table 1 Tab1:** Participant timeline (SPIRIT figure): schedule of enrolment, interventions and assessments

Timepoint	Study period			
	Screening	Baseline	Randomisation	Follow-up 6 month post-randomisation
Enrolment				
Eligibility	X			
Informed consent		X		
Contacts data	X			
Randomisation allocation			X	
Assessments				
Demographic data		X		X
Dynamic indicators of basic early literacy skills (DIBELS) completed by study research assistant (S-RA) in response to answers given by participant		X		X
Reading self-efficacy completed by S-RA in response to answers given by participant		X		X
Carer supporting reading self-efficacy		X		X
EQ5D-3L completed by participant		X		X
The personal well-being index intellectual disability completed by S-RA in response to answers given by participant		X		X
Client service receipt inventory (CSRI) completed by family member/support worker		X		X
Qualitative study—participants				X
Qualitative study—support staff/family carers				X

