#### Progression criteria for a definitive trial

Criteria will inform the decision to progress to a definitive trial, with consideration to issues that may have affected meeting any of these criteria and steps that can be taken to overcome these issues within a full trial. These will be based on a traffic light system with green indicating ‘go without any modification necessary’; amber indicating ‘potential proceed to definitive trial, remedying early issues’; red indicating ‘stop’.**Participant recruitment**: % of participants approached, and who are eligible, consent to the study (and thus are willing to be randomised)Green ≥50%Amber 30≥<50%Red <30%**Individual randomisation possible** (% of total number of settings in which more than one participant is eligible and willing to take part) (NB. Amber/red here may lead to a proposal for a cluster randomised design)Green ≤20%Amber 20>≤40%Red >40%**Rate of recruitment**: % of recruitment target (48 participants) are recruited within the study recruitment periodGreen 100%Amber 70≥<100%Red <70%**Participant retention**: % of participants retained 6 month follow-up data collection timepointGreen 75<>100%Amber 50≥<70%Red <50%**Usual practice**: % of participants in the UP arm of the study who receive an alternative structured programme designed to teach them to read between baseline and 6 month follow-upGreen ≤30%Amber 30>≤50%Red >50%**Fidelity**: Self-rating forms indicate % of READ-IT manual components have been met both across and within sessions.Green 70<>100%Amber 50≥<70%Red <50%**Adherence**: % of participants and their support workers/family carers who adhere to the READ-IT programme (attend training, complete 80 episodes within 20 weeks, meet adherence criteria built into HER® programme)Green >70%Amber 50≥<70%Red <50%**SSC consensus**—considering all progression criteria, feasibility study findings and evidence of whether progression criteria not met can be mitigated, a clear majority of the SSC independent members recommend progression to a definitive trial

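### The feasibility of the reading outcome is to be assessed, but no traffic-light criterion uses it: retention can be green whatever share of those seen have a scorable DIBELS

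*Protocol article*

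**What the plan says.** Under Outcomes, the protocol article states: "The feasibility of using a range of established outcome measures, proposed to test the intervention in a main trial, will be assessed". The list that follows opens with DIBELS and continues with reading self-efficacy, quality-of-life measures and a service-use inventory. The same section puts acceptability of the primary outcome measures among the items reviewed for the secondary objective, but does not say which of the listed measures are primary. The timeline table schedules DIBELS at baseline and at six months.

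Stage 1 includes "an adaptation for online delivery of all measures used in data collection", so the reading test will be used in a newly adapted form.

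The Sample size section gives no power calculation. It justifies 48 participants by precision, using the case "if 80% of participants provide outcome data at follow-up".

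The Progression criteria section sets seven traffic lights with numerical bands:

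- consent among eligible people approached
- settings with more than one eligible and willing person
- recruitment against the target of 48
- retention at six months
- alternative reading programmes in the usual-practice arm
- fidelity
- adherence

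The retention item is the percentage of participants retained at the six-month assessment point. An eighth item, steering committee consensus, has no band. It asks for a clear majority of independent members, "considering all progression criteria, feasibility study findings and evidence of whether progression criteria not met can be mitigated".

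**The concern.** A stated feasibility question has no counterpart among the banded criteria. Whether the reading test can be given and scored in this population, in its adapted form, decides whether a definitive trial of reading is workable. Consent, recruitment, retention, usual practice, fidelity and adherence all have thresholds fixed in advance. Obtaining the reading outcome has none.

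Retention looks like the item that should cover it, but its wording counts people rather than scores, and it does not take over the quantity used in the Sample size section. Even if being retained means having given some follow-up data, nothing requires a DIBELS score to be among those data.

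At stake is what the set of lights conveys. Seven greens could be reported while an unknown share of those followed up have no usable reading score, and no threshold set before the data would mark that share as acceptable or not.

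**Working it through.** **1. The plan's own figure.** Inputs from the Sample size section: n = 48, p = 0.80, 95% confidence.

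Half-width = 1.96 × √(0.80 × 0.20 / 48) = 0.113, giving 68.7% to 91.3%. This reproduces the stated ±11 points (69 to 91%), so the precision statement is sound as a normal-approximation interval. The quantity it describes is the share of participants who supply outcome data.

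**2. The quantities side by side.**

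- Sample size section: participants who supply outcome data at follow-up.
- Progression criteria, retention: participants retained at six months, with no instrument named.
- Outcomes section: feasibility of DIBELS and acceptability of the primary outcome measures, with no threshold attached.

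The first two may be meant as the same thing, but neither asks for a scorable DIBELS. The third appears in none of the seven lights.

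**3. What the retention light shows.** The bands are green above 75%, amber from 50% to below 70%, and red below 50%. The lowest green count is 37, since 36/48 = 75.0% is not strictly above 75% and 37/48 = 77.1% is. The table holds 37 retained and varies how many have a scorable six-month DIBELS. The document gives no figure for this number, so the whole range from 0 to 37 is open and the rows are assumptions.

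| Scorable DIBELS among 37 retained | Without a score | Share of 48 randomised | Retention light as written | Same bands applied to scorable DIBELS |
|---|---|---|---|---|
| 37 | 0 | 77.1% | green | green |
| 36 | 1 | 75.0% | green | no colour (strict reading) |
| 34 | 3 | 70.8% | green | no colour |
| 33 | 4 | 68.8% | green | amber |
| 24 | 13 | 50.0% | green | amber |
| 23 | 14 | 47.9% | green | red |
| 0 | 37 | 0.0% | green | red |

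The fourth column does not change, because the light does not depend on the first.

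**4. The bands.** Green starts above 75% and amber stops below 70%. Counts of 34/48 (70.8%) and 35/48 (72.9%) have no colour, nor does 36/48 on a strict reading. A redefined numerator would inherit this gap.

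**5. Can the missing quantity be estimated?** Yes. DIBELS is scheduled at both timepoints. At 80% scorable among all 48 randomised, the half-width is the 11.3 points of step 1. Among 37 retained it is 1.96 × √(0.80 × 0.20 / 37) = 0.129, or 12.9 points.

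**The case against.** The strongest reply is that the lights only inform the decision. The steering committee must recommend progression by a clear majority and weighs the feasibility findings as a whole; outcome-measure feasibility is a declared part of those findings. The advisory group also reviews them. This stands. A reader might infer that nothing could stop a trial with an unworkable reading outcome, and the document does not support that. What remains is that the safeguard is a judgement with no threshold and no explicit mention of the outcome measures.

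A second reply is that retention at a data collection point, read with the sample size example, naturally means giving follow-up data, and that the exact numerator can be left to the analysis plan. The reading is fair, but it still does not require a reading score. The progression criteria are set out here with their bands, so what each light counts belongs with them.

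A third reply is that the risk is limited upstream. Baseline assessments, which include DIBELS, are completed before randomisation; participants must be able to sound out words; the adapted measures are piloted in Stage 1; and follow-up may be face to face. All of this makes a large loss of scores less likely. It does not supply a completion rate at six months in the randomised sample.

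Three further inferences should be resisted. Nothing says that a form completed only by the supporter would make the adult with intellectual disability count as retained. Nothing in the document supports any particular split between people seen and people with a score. And although feasibility estimates are to inform the later sample size, the article does not say that the retention light will set its attrition allowance, so a biased allowance is not established.

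**Conclusion.** The point holds in a limited form. The feasibility of DIBELS and the acceptability of the primary outcome measures are stated as things to be assessed, yet none of the seven banded criteria uses an outcome score, and the measures to be judged are not identified. Retention can be green at 37/48 (77%) with anywhere from 0 to 37 scorable reading tests, that is, 0% to 77% of those randomised. Only the unbanded steering committee item could react to this.

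The conclusion rests on the wording of the criteria, not on a forecast. It makes no claim that many scores will be missing, and it does not question the sample size figure, which reproduces. It is a fault in a stated decision rule that should be corrected before data are seen, not one that invalidates the study.

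**What to change.** 1. Make the retention bands contiguous first, so that every percentage from 0 to 100, including 70% to 75%, has a colour.
2. Name DIBELS as the candidate primary outcome whose acceptability is to be judged.
3. Define the retention numerator as participants with a scorable six-month DIBELS, with all randomised participants as the denominator. Alternatively, keep retention as attendance and add a separate DIBELS completeness light with its own contiguous bands.
4. Report separately those who attended at six months but have no scorable DIBELS, so that loss of people and failure of the measure can be told apart.

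The change is one of wording. DIBELS is already scheduled at baseline and six months, so there is no added burden on participants and no change to the sample size. The price is a retention figure that may look less favourable than one based on attendance.
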